### Study Setting

The Carolinas RESPOND study focuses on North Carolina and South Carolina, with collaboration among academic and public health partners in both states (see Figure 1). The eSNS intervention described in this protocol is planned for the Charlotte region, covering a 5-county area in the North Carolina Department and Health and Human Services’ (DHHS) Field Services Region II, which includes the EHE priority jurisdiction [28] of Mecklenburg County (with star in Figure 1). This region directly borders the Midlands region of South Carolina, one of 7 US states with a disproportionate burden of HIV in rural areas [26]; the regions are connected by Interstate 77, which runs from Charlotte, North Carolina, to Columbia, South Carolina (see diamond in Figure 1). Although implementation is focused on the Charlotte region, our eSNS will follow networks that may cross both states because of Charlotte’s geospatial proximity to South Carolina. Due to comparable demographics and HIV epidemiology [27], North Carolina DHHS’s Field Services Region IV, the 11-county area surrounding the Raleigh, North Carolina metropolitan area, was chosen as a “control” region against which outcomes in the Charlotte, North Carolina “intervention” region will be compared.

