### Study Design

We designed a 3-phase process (see Figure 2) to develop, implement, and evaluate eSNS using a quasi-experimental, nonrandomized hybrid type 1 effectiveness-implementation design [34]. This design allows for evaluation of both eSNS effectiveness and the intervention delivery process. Phase 1 (preimplementation), which involved establishing a community advisory group and collecting mixed methods data to inform adaptations to SNS procedures, concluded in August 2024. Analyses of Phase 1 data, which are ongoing, aim to understand the structural, spatial, and network factors that influence HIV services engagement among the study’s priority groups, plus barriers and facilitators to eSNS implementation. In Phase 2, eSNS will be implemented in the Charlotte region over a 3-year period (2025‐2027). In Phase 3, we will evaluate the impact of eSNS on HIV services use compared to standard-of-care partner services delivered in the Raleigh, North Carolina metropolitan region [27] (see Figure 1).

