#### Effectiveness Evaluation

Intervention effectiveness will be assessed by comparing the 5-county Charlotte region to another urban North Carolina region, Raleigh, with similar demographics (see Figure 1). The metropolitan region surrounding Raleigh has the second-largest population in North Carolina, after Charlotte [47]. The primary effectiveness measures are the number of HIV-negative individuals linked to PrEP and the individuals living with HIV who are linked to care per index person from a priority network. Index persons in the intervention region (Charlotte) priority networks will be compared to index persons in the control region (Raleigh) priority networks, who receive standard-of-care partner services. Partner services are standardized among all North Carolina DHHS Field Service regions [48]. We will use a regression point displacement design (RPDD) [49] to assess the impact of eSNS on trends in our primary effectiveness measures between regions over the intervention period; the effective reproduction number for HIV will also be calculated over this period. Measures will be collected for each region at a preintervention baseline (2 years before), postintervention (6 months after), and during implementation for interim analyses at 6-month intervals. Because state HIV surveillance data is available in both the Charlotte and Raleigh regions from the baseline timepoint to a postintervention timepoint, RPDD provides statistical power to estimate the effect of eSNS when aggregating at a group level (index persons from priority networks) [50].

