## Results

The study was funded in July 2022. The initial protocol for phase 1 was approved by the IRB in October 2022, and a modification detailing eSNS intervention procedures for Phase 2 was approved in June 2024. As of December 2024, we have completed the initial phase 1 formative assessments. We launched participant recruitment for eSNS in March 2025. Baseline analyses of HIV molecular epidemiology across North Carolina and South Carolina remain pending execution of data sharing agreements in both states.

Our preliminary research findings and guidance from our CAG and phase 1 identified several recommendations for adaptation and implementation of eSNS. An overarching theme in our qualitative data was the importance of fostering trust through partnerships with CBOs. This led us to develop procedures for supplementing participant recruitment of potential ambassadors beyond partner services clients in priority networks (eSNS step 1) and for facilitating HIV services linkage at local CBOs and clinics (eSNS step 4). Formative qualitative analyses also identified recommendations to address the experience of our key populations with research engagement—specifically by considering strategies to alleviate research fatigue and to ensure that our key populations are represented among the study team. Our CAG recommended opening study participation to members of the Latin community, which is increasingly affected by HIV in the Charlotte area. The amount of overlap between Black and Spanish-speaking Latin sexual networks is currently unclear. To address this, we began offering the PNS in Spanish during phase 1 and expanded the study’s key population to include both Latin and Black GBMSM and transgender women. In phase 2, English-speaking Latin persons will be included as ambassadors. Future intervention scale-up will be needed to adapt eSNS to Spanish-speaking Latine persons.

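### One pre-launch baseline per region gives no pre-launch slope, so any existing divergence between Charlotte and Raleigh would be credited to eSNS in an analysis of trends

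*Protocol article*

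**What the plan says.** All references are to the Protocol article.

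- **Design (Study Design).** The evaluation is described as "using a quasi-experimental, nonrandomized hybrid type 1 effectiveness-implementation design", and "eSNS will be implemented in the Charlotte region over a 3-year period", 2025 to 2027.
- **Regions (Study Setting).** Raleigh "was chosen as a “control” region against which outcomes in the Charlotte, North Carolina “intervention” region will be compared". The reason given is comparable demographics and HIV epidemiology. Effectiveness Evaluation adds that partner services are standardized across the state's regions.
- **Analysis target (Effectiveness Evaluation).** A regression point displacement design is used "to assess the impact of eSNS on trends in our primary effectiveness measures between regions over the intervention period".
- **Schedule (same section).** "Measures will be collected for each region at a preintervention baseline (2 years before), postintervention (6 months after), and during implementation", the last for interim analyses every 6 months.
- **Data (same section).** "state HIV surveillance data is available in both the Charlotte and Raleigh regions from the baseline timepoint to a postintervention timepoint". The baseline is again in the singular. Table 1 lists surveillance data as the source of both primary measures.
- **Launch (Results).** "We launched participant recruitment for eSNS in March 2025".

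The article mentions no second pre-launch value and no check or assumption about pre-launch trends.

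**The concern.** The target is a difference in trend, but the schedule gives a time series only once eSNS is running. One value before launch can remove a standing difference between the regions. It carries no information on whether the gap was widening or narrowing. The half-yearly values cannot supply that information either, because every one of them is taken under exposure.

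In a nonrandomized comparison of two regions, unequal prior trends are a leading alternative explanation for a difference at the end. Similar demographics and a standardized service make equal levels plausible; they do not establish equal trends. Having a single control region makes this worse: there is no scatter among control regions against which ordinary regional drift could be seen.

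The article also gives some reason to look. With launch in March 2025, a baseline two years earlier falls around March 2023. The Charlotte-area community advisory group was formed in August 2023 and the formative interviews ran into 2024, both between the baseline and launch. Whether they moved any outcome is unknown, but the schedule could not reveal it.

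**Working it through.** **1. The plan's own figures (Sample Size and Power Estimates)**

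- Network index before: 100 contacts / 60 persons = 1.67, stated as 1.7 (SD 1.8).
- Network index with eSNS: (80 × 1.7 + 20 × 5.0) / 80 = 2.95, stated as 3.0. Planned rise: 3.0 − 1.7 = 1.3.
- Power, two means, two-sided 0.05, 30 per group: Φ(1.3 / (1.8 × √(2/30)) − 1.96) = Φ(2.80 − 1.96) = 0.80. The stated 80% is reproduced if 60 is the total over two groups. This calculation has no term for a trend.

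This network index counts contacts and peers, while the primary measures count persons linked per index person. The 1.3 is used below only as the plan's own yardstick.

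**2. Time from baseline to the post value**

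- Baseline as a point two years before launch: 2 + 3 + 0.5 = 5.5 years (about 5.3 if delivery runs from March 2025 to December 2027).
- Baseline as a two-year window, centred one year before launch: 1 + 3 + 0.5 = 4.5 years.

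A window reported as one value still gives no slope.

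**3. Spurious effect = yearly divergence × gap (divergence rates are assumptions)**

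| Divergence, index units/year | 4.5 years | 5.5 years | Share of 1.3 |
|---|---|---|---|
| 0.05 | 0.23 | 0.28 | 17-21% |
| 0.10 | 0.45 | 0.55 | 35-42% |
| 0.20 | 0.90 | 1.10 | 69-85% |

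To mimic the whole planned rise, the divergence would have to be 1.3 / 5.5 = 0.236 a year, or 1.3 / 4.5 = 0.289. That is 14% to 17% of 1.7 every year. If all post-launch half-years were averaged and set against a two-year window, the centres would be 1.00 year before and 1.75 years after launch. The gap is then 2.75 years and 0.10 a year gives 0.275.

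**4. What slope adjustment would cost**

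Assumptions: 40 index persons per region per half-year (80 a year, Raleigh taken as equal), SD 1.8, independence. There are four half-years before launch, six during and one after. The variance of the regional gap per half-year is v = 2 × 1.8² / 40 = 0.162.

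- No trend term: SE = √(0.162 × (1/4 + 1/7)) = 0.25.
- Common linear trend in the gap: the squared correlation of time with the launch indicator is 19.25 / 27.5 = 0.70, so SE = 0.252 / √0.30 = 0.46. Bias from a steady divergence is zero. Power for 1.3 is Φ(1.3/0.46 − 1.96), about 0.81.
- Slope from the four pre-launch values alone: SE of the slope = √(0.162 / 1.25) = 0.36 a year. Projected to the post-launch centre, 2.75 years on: SE = √(0.162 × (1/4 + 2.75²/1.25 + 1/7)) = 1.02. Power for 1.3 is about 0.25.
- Eight pre-launch values (four years): SE of the slope = √(0.162 / 10.5) = 0.12. Projected 3.75 years: SE = √(0.162 × (1/8 + 3.75²/10.5 + 1/7)) = 0.51.

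**The case against.** **The baseline phrase is ambiguous.** It may mean a two-year period, and nothing says the period will be collapsed to one value. The ambiguity is real, but the next sentence of the article speaks of a baseline timepoint, and half-yearly collection is assigned only to implementation. Followed as written, the schedule gives no pre-launch slope under either reading.

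**Model terms belong in a SAP that is not shown.** This is fair for the model terms and is not held against the article. The measurement schedule, however, is stated, and it does not fit the stated target.

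**The weakness comes largely from having one control region.** This stands in part. With several controls, ordinary drift would enter the scatter around the regression line and widen the error; bias would remain only if Charlotte's drift were unusual. The two problems overlap.

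**Nothing shows that the regions diverged, and the drift rates have no anchor.** This stands. A reader might infer that the trial will report a false effect, or that Charlotte and Raleigh were on different courses before launch. The documents support neither: they hold no trend data for either region. Nor is a pre-launch trend the only safeguard. Peers are tied to ambassadors by referral codes, so the direct eSNS yield can be counted beside the regional contrast, although the primary measures come from surveillance.

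**Slope adjustment is expensive.** This stands, and it decides where the adjusted estimate belongs.

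**Conclusion.** The point holds in conditional form. As scheduled, the comparison cannot separate a divergence already under way from an effect of eSNS on trends. If there was such a divergence, at 0.05 to 0.20 index units a year it would contribute about 0.23 to 1.10 to a baseline-to-post contrast planned around 1.3. It would take roughly 0.24 to 0.29 a year to reproduce the planned effect in full. These sizes rest on assumed, steady rates, on a gap of 4.5 to 5.5 years, and on borrowing the network-index scale for the primary measures. The single control region aggravates the problem. The case for change does not depend on divergence being likely: the article says surveillance data exist for both regions from baseline onward, so the matter can be examined.

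**What to change.** 1. State whether the baseline is a time point two years before launch or a two-year window.
2. Extract both surveillance-based primary measures, in both regions, at the same 6-month intervals before launch: at least four values per region, and more if surveillance allows.
3. Report the pre-launch difference in slope between the regions with its confidence interval.
4. Keep the planned comparison as primary and add a sensitivity estimate that adjusts for the pre-launch slope. Qualify the conclusion if the slopes differ.

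**Cost.** A few more cuts of surveillance data and some analysis wording; no participant procedure changes. The price is precision in the sensitivity estimate: under the assumptions above, an SE of about 0.46 instead of 0.25 with a common linear trend, and about 1.0 if a slope from only four values is projected forward. That is why it should not replace the primary analysis. With four values the slope difference itself has an SE of about 0.36 a year, wider than any divergence considered here. A non-significant difference should therefore not be reported as evidence of parallel trends. Eight values would bring that SE to about 0.12, so a longer series is worth asking for.

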#### Sample Size and Power Estimates

Of approximately 280 new HIV diagnoses reported annually in the Charlotte region, 80 would meet criteria for index persons eligible to be assigned to DIS coaches for routine partner services (including 20 acute HIV infection). From these 80 index persons, we estimate that 25% of contact networks reached through partner services will yield an enrolled ambassador (n=20). Based on partner services data previously reported to North Carolina DHHS, 100 contacts were elicited from 60 persons who were newly diagnosed with HIV in the Charlotte region from 2016 to 2019, yielding a network index of 1.7 (SD 1.8). With a peer outreach network index of 5.0 per ambassador (based on previous reports [22]), this would increase the overall network index in the Charlotte region from 1.7 to 3.0. We estimate an 80% power with alpha=.05 to detect a significant effect of eSNS on network index with 20 ambassadors enrolled per year for 3 years (n=60). Of note, we do expect that ambassadors’ referral networks will have a bimodal distribution—with most having a low number of peers while a few will yield a high number of peers.

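### The 80% power pairs an effect averaged over 240 index persons with a count of 60 ambassadors, and the only SD given comes from partner services without eSNS

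*Protocol article*

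**What the plan says.** All the inputs stand in the protocol article, Sample Size and Power Estimates.

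- Index persons: of the yearly diagnoses in the Charlotte region, "80 would meet criteria for index persons eligible to be assigned to DIS coaches for routine partner services".
- Ambassadors: "we estimate that 25% of contact networks reached through partner services will yield an enrolled ambassador (n=20").
- Baseline: "100 contacts were elicited from 60 persons who were newly diagnosed with HIV in the Charlotte region from 2016 to 2019". The section summarises these data as "yielding a network index of 1.7 (SD 1.8"). These are contacts named in partner services before eSNS existed.
- Effect: at 5.0 peers per ambassador, "this would increase the overall network index in the Charlotte region from 1.7 to 3.0".
- Power: "We estimate an 80% power with alpha=.05 to detect a significant effect of eSNS on network index". The same sentence ties this to recruitment, "with 20 ambassadors enrolled per year for 3 years (n=60").
- Spread: the section closes by expecting that ambassadors' "referral networks will have a bimodal distribution", with many low yields and a few high ones.

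The Effectiveness Evaluation section sets the comparison as index persons in Charlotte against index persons in Raleigh, where standard partner services apply. The article gives no number of index persons for Raleigh and does not say which test, sidedness or SD lies behind the 80%.

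**The concern.** An effect size, a sample size and an SD belong together only if they describe the same unit. Here the effect is per index person, while the sample size counts ambassadors, who come from a quarter of the index persons' networks and exist in one region only. The SD describes index persons before any ambassador was added.

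The intervention itself adds spread: about a quarter of index persons gain several peers and the rest gain none. The section expects that gain to be uneven, yet it shows no allowance for it.

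This is the article's only statement of power. As written, a reader cannot tell which comparison has 80% power.

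**Working it through.** **Inputs.** From the sample size section: 80 index persons and 20 ambassadors a year, three years, 5.0 peers per ambassador, baseline mean 1.7, SD 1.8, alpha 0.05. Assumed because not stated: two-sided test, normal approximation, independent index persons, and equal numbers in Raleigh unless shown otherwise.

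**1. Which unit gives 3.0?** Averaged over index persons: 1.7 + (20/80) × 5.0 = 2.95, which rounds to 3.0. For a network that yields an ambassador, the expected value would be 1.7 + 5.0 = 6.7. So the effect is per index person, and the matching number is 80 × 3 = 240, not 20 × 3 = 60.

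**2. Reproducing the 80%.** Power = Φ(difference/SE − 1.96), with SE = 1.8 × √(1/n₁ + 1/n₂) and difference 3.0 − 1.7 = 1.3.

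| n₁ v n₂ | SE | difference/SE | Power |
|---|---|---|---|
| 30 v 30 | 0.465 | 2.80 | 79.9% |
| 20 v 60 | 0.465 | 2.80 | 79.9% |
| 60 v 60 | 0.329 | 3.96 | 97.7% |
| 240 v 240 | 0.164 | 7.91 | over 99.9% |

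The stated figure therefore appears if 60 is the total of two groups of 30, or if one year's 20 ambassadors are set against the 60 historical persons. Neither is what the text says: it counts 60 ambassadors over three years, all in Charlotte.

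**3. The SD under eSNS.** Let a share 0.25 of index persons gain peers, with mean 5 and SD s, and let the rest gain none. If the gain is independent of the baseline contacts, the Charlotte variance is

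1.8² + 0.25 × 0.75 × 5² + 0.25 × s² = 3.24 + 4.69 + 0.25 s².

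The article gives no s, so a range is assumed:

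- s = 0 (every ambassador brings exactly 5): variance 7.93, SD 2.82
- s = 5: variance 14.18, SD 3.77
- s = 10: variance 32.93, SD 5.74

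Even the most even yield possible puts the SD well above 1.8, and the uneven yield that the section expects raises it further.

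**4. Power on the consistent unit.** With 240 index persons per region, the unrounded difference 1.25, and Raleigh at SD 1.8, SE = √((Charlotte variance + 3.24)/240):

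- s = 0: SE 0.216, 1.25/SE = 5.79, power over 99.9%
- s = 5: SE 0.269, 1.25/SE = 4.64, power 99.6%
- s = 10: SE 0.388, 1.25/SE = 3.22, power 89.6%

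These figures leave out any variation between regions.

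**The case against.** Four points can be made for the plan.

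- **The figure does reproduce.** The section's own difference and SD give 79.9% at 30 v 30, and 30 + 30 = 60. A reader might infer from the mismatch of units that the 80% cannot be obtained from its inputs at all. That goes too far. What remains is that the reading which reproduces it does not fit the text, because standard partner services in Raleigh have no ambassadors to make up a second 30.
- **The SD used is not stated.** The 1.8 is reported only as the spread of the 2016 to 2019 data. At 60 v 60, a common SD of about 2.5, or 1.8 in Raleigh and about 3.1 in Charlotte, would also give 80%. This stands, so the criticism of the SD is conditional on 1.8 having been used. The mismatch of units does not depend on it.
- **The 60 may be an enrolment condition.** It can be read as the recruitment that produces an index of 3.0, with index persons as the analysis unit. That is a fair reading, but then the power statement has no sample size. With 240 per region, a common SD of about 5.1 would be needed to bring power down to 80%, and nothing in the section points to that.
- **The planned analysis is a regression point displacement design.** A two-sample calculation is only a benchmark, and an article may leave the power method to the full protocol. This stands as a limit on the percentages. It does not explain why an effect per index person is attached to a count of ambassadors.

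**Conclusion.** The point holds as a mismatch of units and an unsuitable or unstated SD. The effect of 1.7 to 2.95 belongs to 240 index persons, while the stated number is 60 ambassadors. At a difference of 1.3 and SD 1.8, the 80% fits neither 60 v 60 nor 240 v 240. If 1.8 was used, the SD in Charlotte is understated by at least 1.0 (2.8 against 1.8), given independence of baseline contacts and peer yield.

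A reader might go on to infer that the study is underpowered. The documents do not support that. On the unit that the article itself compares, simple power is about 90% or more across the range of s tried. That result assumes 240 index persons in Raleigh and ignores variation between regions, which cannot be estimated with one region per arm.

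The calculation also concerns contacts per index person. The primary measures are persons linked to PrEP or to HIV care per index person, so neither the stated 80% nor the recalculated figures describe the power for those.

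**What to change.** Restate the power with the index person as the unit: 240 in Charlotte and the expected number in Raleigh. Take the Charlotte variance as 1.8² + 0.25 × 0.75 × 5² + 0.25 × s², and show the result over a stated range of s, the SD of peers per ambassador. Name the test and its sidedness. Keep the 60 ambassadors as the recruitment target only.

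Add one sentence saying that the figure concerns contacts per index person, not the primary linkage measures, and takes no account of variation between the two regions.

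The cost is one recalculation and a few replaced sentences. The stated 80% will probably change, but no study procedure does.

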#### Process Evaluation

Process measures will be routinely collected during phase 2 to examine implementation facilitators and barriers concurrent to intervention delivery, which will inform future scale-up (see Figure 3). We will use a triangulation protocol to integrate mixed-methods data from qualitative and quantitative sources [52]. Guided by the CFIR [38], we plan to conduct in-depth interviews with 2 ambassadors per intervention year (total of 6 interviews with ambassadors) and annual interviews pre- and postimplementation with the 2 DIS coaches (total of 4 interviews). Interviews will explore DIS coach and ambassador perceptions across three CFIR domains: including (1) the adaptability and complexity of the intervention (intervention characteristics); (2) the structural characteristics, communications, relative priority of eSNS within a state public health agency delivering partner services (inner setting*)*; and (3) the characteristics of DIS coaches’ and ambassadors’ self-efficacy and knowledge (individuals). To understand additional factors that may influence intervention delivery, we developed a survey instrument administered to ambassadors after concluding peer outreach. This instrument will incorporate items from previously validated scales to quantitatively assess self-efficacy and intervention acceptability [53], HIV-related stigma (for ambassadors living with HIV) [54,55], experiences of discrimination [56], and gender identity and connectedness with the LGBTQ+ community [57,58].

Routine program monitoring data will be analyzed at 6-month intervals to assess whether eSNS is being delivered as intended (fidelity) over the intervention period and the extent to which eSNS as designed mitigates social barriers to HIV services engagement. We will monitor program delivery along each step in eSNS. Fidelity measures include the number of potential ambassadors identified per year (step 1), the length of the initial coaching session (step 2), the number of follow-up coaching contacts each DIS coach holds with each ambassador, and the length of time between peers contacting the study team and screening (step 4). A full set of monitoring measures is provided in Multimedia Appendix 2.

